#### Secondary outcome measure

In addition to the point prevalence measures, six and 12 month continuous abstinence will be assessed at six and 12 month follow up as recommended by the SRNT [42].

#### Moderating factors

These items will be collected at baseline, used as part of the intervention print-out, and included in multivariate analysis. ***Sociodemographic characteristics ***will include age, gender, marital status, housing status, income, education, postcode. ***Nicotine dependence ***will be measured by the Heaviness of Smoking Index (HSI), a two-item short form of the Fagerstrom Tolerance Questionnaire [45]. The HSI scores range from 0-6 and are calculated by summing the points for 1) time to first cigarette smoked after waking (in minutes) and 2) number of cigarettes smoked per day. Higher HSI scores indicate more dependence on nicotine. ***Quit attempts***. A commonly used [16,17] item which asks "How many serious attempts to stop smoking have you made in the last 12 months? By serious attempt I mean you decided that you would try to make sure you never smoked again. Please include any attempt that you are currently making and please include any successful attempt made within the last year". ***Use of cessation aids***. Clients who have made a serious quit attempt will be asked about treatments they had used in their most recent quit attempt. A single item developed by Shiffman et al [16] will list various pharmacological, behavioural and alternative smoking cessation aids. ***Partner smoking behaviour***. One item [46] will assess partner smoking behaviour: "Does your partner smoke?" (response options: yes, yes but stopping with me, no ex-smoker, no never smoked, N/A). ***Depression***. A recent meta-analysis indicates that the Patient Health Questionnaire (PHQ) has sensitivity of 80% and specificity of 92% in diagnosing major depression [47]. The two-item PHQ2 is recommended by the US Preventive Services Taskforce for depression screening and will ask "Over the last 2 weeks have you felt down, depressed or hopeless?" and ".. have you felt little interest or pleasure in doing things?". ***Financial stress ***will be measured using a scale developed by Siahpush et al [9,48] and previously used as a predictor of smoking behaviour. It includes items asking "In the last six months, did any of the following happen to you because of a shortage of money?" followed by six options.

#### Process measures. *Acceptability of intervention*

At six-month follow-up staff and clients will also be asked to rate the acceptability, usefulness and perceived effectiveness of the smoking cessation intervention. ***Staff and client intervention checklists. ***Completed staff and client printed checklists of intervention strategies offered, accepted, refused, and provided will be compared at the conclusion of the trial to measure exposure and adherence to the intervention. ***Costs. ***Relevant costs of delivery of the intervention and estimates of costs to the community service sector including staff time will be identified, collected and valued to allow a cost-benefit analysis from the service provider perspective. Savings in terms of cessation rates and savings in health care costs will be analysed.

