### Sample size

A sample of 200 participants per group at 12 months will allow detection of a difference in smoking cessation rates of 8% between groups at 12 months (slightly smaller difference of 7% can be detected at 1 month), based on 5% smoking cessation in the usual care group and 13% in the intervention group, at 5% significance level and 80% power. This effect size is achievable and important from a population-effect perspective. Non-randomised and observational studies using less intensive smoking cessation interventions within disadvantaged groups have demonstrated high cessation rates [25,28-30]. Estimating that 30% of the sample are lost to follow-up (10% at each of one, six and 12 months), 290 patients per group will be recruited at baseline. The Centre receives approximately 50 new clients a week and 50% of those are for ongoing counselling care. All new clients will be eligible to complete the baseline touch screen computer survey. Over a 12-month recruitment period, 1,300 new clients will attend for counselling services. Staff estimate that 60%-90% of clients are current smokers. Assuming a median value of 75%, there will be approximately 975 eligible clients during the study period. Assuming a consent rate of 60% [28-31], 585 individuals will consent to participate in the study.

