### Recruitment and randomisation

A trained RA will be situated in the Centre communal waiting room during recruitment. The RA will approach all clients entering the Centre, ascertain eligibility, and seek written consent. A two-stage consent process will be used. First, the RA will inform clients that the study aims to expand the services provided by the Centre and involves completing a health survey on a touch screen computer and that their case-worker may discuss health issues with them. When they complete the survey, if they reported to smoke, they will be informed, on-screen, that a study for smokers is being conducted and that the RA will seek their consent to participate in the smoking study. They will be told that participation in the smoking study will involve their counsellor or case worker possibly discussing quitting with them, and that they will be asked to return to the Centre in one, six and 12 months time to complete the survey and conduct a breath test for carbon monoxide (CO) measurement. Consenting clients will be assisted in the use of the touch screen survey. The RA will review the clients' smoking status on a touch screen survey print-out and randomly allocate participants who are current smokers to the control or intervention group depending on whether it is an intervention or control week. Intervention or control times will be randomly allocated in blocks of four by a computer generated randomisation procedure. Clients who are not smokers will not participate further in the study.

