#### The Case Worker Sessions

The intervention will be implemented over one or two face-to-face visits (each two weeks apart) which will commence immediately following baseline survey completion, followed by at least two phone contacts (one week apart). This intervention will constitute an add-on to clients' usual regular counselling visits, reducing additional costs to the Centre and to clients. If a client requires further contact, staff will provide further quitting assistance and record what they delivered on their checklist. Clients who do not return within the two week timeframe will be contacted by the caseworker by telephone. Appendix 1 provides a session by session description of the intervention.

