#### Acceptability

The proportion of participants reporting that the intervention was acceptable, useful, and effective will be determined with 95% confidence intervals.

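### Clients rate acceptability only at the six-month return visit, when planned losses are twice those at the existing one-month survey, so the reported proportion describes returners and can be biased

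*Protocol article*

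**What the plan says.** - **Time of rating.** Protocol article, Process measures: "At six-month follow-up staff and clients will also be asked to rate the acceptability, usefulness and perceived effectiveness of the smoking cessation intervention". No other time is given for this rating.
- **Scheduled contacts.** The Case Worker Sessions section plans "one or two face-to-face visits (each two weeks apart) which will commence immediately following baseline survey completion". After these visits, staff make a minimum of two telephone calls, spaced a week apart. Contact beyond this depends on need: "If a client requires further contact, staff will provide further quitting assistance and record what they delivered on their checklist".
- **How follow-up happens.** Recruitment and randomisation tells clients that "they will be asked to return to the Centre in one, six and 12 months time to complete the survey". Rating at a follow-up therefore means coming back to the place that delivered the intervention, and a survey at one month is already planned.
- **Expected losses.** Sample size: "Estimating that 30% of the sample are lost to follow-up (10% at each of one, six and 12 months"), with 290 recruited per group.
- **Analysis.** Acceptability section: "The proportion of participants reporting that the intervention was acceptable, useful, and effective will be determined with 95% confidence intervals".

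**The concern.** A client who has left by six months never rates the intervention. Dislike of the caseworker sessions, or abandoning them, is a plausible reason for not returning, so the missing ratings may differ from those obtained. The plan recognises a similar risk for smoking status: its intention-to-treat analysis treats clients who miss follow-up as still smoking. That rule is stated for the efficacy outcomes and does not extend to acceptability.

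A confidence interval computed on the returners reflects sampling error only. It would look equally precise whether or not the missing clients differed. Those who do answer are also recalling sessions several months old, knowing whether they have quit or relapsed.

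At stake is how well a process measure describes the clients who were offered the intervention, and so how useful it is to services considering adoption. An early rating cannot be collected once a client has passed one month.

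**Working it through.** **1. The plan's own figures.** For 5% v 13% cessation, two-sided 5% significance, 80% power, pooled variance and no continuity correction, the requirement is 200 per group (power at 200 is 80.1%), as stated. With 30% loss, 200 / 0.70 = 286, close to the stated 290. The loss assumption is thus consistent with the recruitment target and can be used below.

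**2. Time from last scheduled contact to rating.** Assume 0 to 2 weeks between the last visit and the first call (the article does not say), a second call one week later, and six months = 26 weeks.
- Two visits (weeks 0 and 2): last call at week 3 to 5.
- One visit (week 0): last call at week 1 to 3.
- Gap to the rating: 26 − 5 = 21 weeks up to 26 − 1 = 25 weeks, or 4.8 to 5.8 months at 4.345 weeks per month.

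The minimum schedule therefore ends about five months before the rating.

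**3. Expected raters among 290 intervention clients.**
- One month: 290 × 0.90 = 261, so 29 not rating.
- Six months: 290 × 0.80 = 232, so 58 not rating. If losses compound, 290 × 0.81 = 235.

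**4. Selection bias.** Bias = proportion lost × (rate in returners − rate in non-returners). The gaps are assumptions; the documents give none.

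| Assumed gap | Bias at six months (20% lost) | Bias at one month (10% lost) |
|---|---|---|
| 0 points | 0 | 0 |
| 10 points | 2 points | 1 point |
| 20 points | 4 points | 2 points |
| 30 points | 6 points | 3 points |
| 40 points | 8 points | 4 points |

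For the same gap, the earlier rating halves the bias. A negative gap reverses the sign.

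**5. Comparison with the reported precision.** Assume 80% of responders find the intervention acceptable.
- Six months: 1.96 × √(0.8 × 0.2 / 232) = 5.1 points.
- One month: 1.96 × √(0.8 × 0.2 / 261) = 4.9 points.

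A gap of 5.1 / 0.20, about 26 points, makes the six-month bias as large as the half-width.

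**6. Extreme bounds over all 290, same assumed 80%.**
- Six months: 0.8 × 0.8 = 64% if no non-responder approves; 64% + 20% = 84% if all do.
- One month: 0.8 × 0.9 = 72%; 72% + 10% = 82%.

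These are limits, not expected values, and both extend above 80% as well as below it.

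**The case against.** The strongest defence is that six months is a reasonable time to judge the whole package. The calls are a minimum, further help is given on request, and Appendix 1 adds drop-in and phone-in sessions, Quitline referral and Life Skills courses. By the timeline above, a client's last scheduled call could fall after a one-month survey. This stands, and it is a reason not to replace the six-month rating. It does not argue against an additional earlier one.

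The direction is also open to challenge. A reader might infer that the result is bound to be too favourable, or that knowing one's quit status inflates it. The documents support neither. Nothing in them says that dissatisfied clients return less often, and clients also attend the Centre for other services. The plan expects 13% cessation in the intervention group at 12 months, so most six-month raters may still be smoking, which could lower ratings of usefulness and perceived effectiveness. Quit status is also known at one month, so moving the rating would not remove that influence. Recall error has no known sign.

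Other process data exist. Staff rate acceptability without depending on client return, and the checklists record components offered, accepted, refused and provided. These give partial information on clients who later leave, but the article uses the checklists for exposure and adherence, and neither source is the client's own rating.

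Finally, the handling of non-responders in a descriptive measure is commonly left to a fuller document. That is fair: its absence from the article is not the fault here. The time of rating is what the article itself fixes.

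**Conclusion.** The point holds as a minor one. With a single client rating at six months, the acceptability proportion will describe about 80% of intervention clients, where the existing one-month survey would reach about 90%. The bias is probably upward if dissatisfied clients return less often: 2 to 8 points for assumed gaps of 10 to 40 points, against 1 to 4 points at one month. With no gap it is zero. These sizes rest on the plan's own loss estimate and on the assumed gaps; the half-width of about 5 points rests on an assumed 80% approval.

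It would go too far to say that the trial's case for use in standard care depends on this rating. The Discussion presents the setting's acceptability as a premise and makes implementation conditional on the intervention being effective. The rating informs implementation, and the efficacy comparison is unaffected.

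**What to change.** - In Process measures, add the client items on acceptability, usefulness and perceived effectiveness to the existing one-month survey for intervention clients.
- Keep the six-month rating, described as the view of the whole package including drop-in and phone support.
- In the Acceptability analysis, report each proportion twice: among responders, and over all intervention clients with non-responders counted as not reporting it acceptable. Label the second as a lower bound, since it is an extreme assumption and not an estimate.

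The cost is a few items on a survey that clients already complete and a sentence or two in the analysis section. The one-month survey becomes slightly longer, some clients will rate before their last scheduled call, and the reported figure may be lower.

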### Data Analysis

Data will be stored in Access databases and exported for analysis to SAS. The distribution of all variables will be checked for normality, with non-parametric statistics used when appropriate. Characteristics of study participants will be compared between intervention groups using the chi-square test for categorical variables and the t-test or a non-parametric equivalent for continuous variables.

#### Efficacy of intervention

To assess the efficacy of the intervention at smoking cessation (validated by expired air CO), the intervention and control groups will be compared on each of the primary outcomes using chi-square analysis: 1) proportion abstinent last 24 hours (validated) at one, six and 12 months; and 2) proportion abstinent for seven days at one, six and 12 months. Univariate analyses will be undertaken to examine factors associated with each of the two outcomes, using the chi-square test for categorical variables and the t-test or a non-parametric equivalent for continuous variables. In addition to the primary analysis, intention-to-treat analysis will also be undertaken whereby clients who fail to complete follow-up in the study will be considered to be continuing smokers. Multiple logistic regression analyses will be used to compare outcomes between the two intervention groups while adjusting for prognostic variables and potential confounders (sociodemographic, financial stress, depression, and other variables collected).

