### The personal and environmental context of smoking and quitting in disadvantaged groups

Qualitative research has shown that smoking is often deeply embedded in the lives of disadvantaged smokers because they live, socialise and/or work with other smokers, making it more difficult to refrain from smoking [7]. It has also been shown that smoking is influenced by unfavourable life trajectories such as childhood and educational disadvantages [8]. Smokers from more deprived socioeconomic groups also have higher levels of stress which can play a role in relapse because smokers often use smoking to cope with stressful aspects of their lives [9]. Importantly, studies have described the higher rates of nicotine dependence in smokers from more deprived socioeconomic groups [10], and past research has found nicotine dependence is a predictor of failure of attempts to stop smoking [11]. These factors suggest that smokers from lower socioeconomic groups may need strategies that address their unique life circumstances.

Studies have found that socially disadvantaged smokers are as interested in and as motivated to quit as other smokers [12,13]. However, some important differences in quitting behaviours between socioeconomic groups exist. Lower socioeconomic groups tend to receive less physician advice to quit, [14] access telephone quitlines less, even during mass media campaigns [15] and use fewer pharmacotherapies [16]. Also, although the number of quit attempts is similar across groups, it is achieving quitting success that is difficult for those in lower socioeconomic groups [17]. It appears smoking and smoking cessation in disadvantaged groups are complex behaviours with deeply embedded interacting influences. Multifaceted and intensive interventions addressing multiple motivators may be appropriate approaches for further research.

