### Measures

#### Primary outcome measure - *client validated self-reported smoking cessation*

There will be two primary outcome measures obtained at one, six and 12 month follow-up: 1) 24-hour CO validated self-reported smoking cessation and 2) 7-day self-reported smoking cessation. These follow-up time periods and measures of smoking cessation have been recommended by the Society for Research on Nicotine and Tobacco (SRNT) workgroup [42] for measuring smoking cessation. Seven-day smoking cessation will be defined as abstinent for the past seven days at one, six and 12 months respectively. Seven-day point prevalence abstinence is a common and recommended cessation outcome and has the highest concurrent validity of a range of cessation measures [43]. ***Biochemical *v*erification of self-report: ***General population reports and some clinical trial based studies show that misreporting tends to be low, around 5% [38]. Little is known regarding the misreporting rate of smoking status in this population. Thus, this study will use biochemical validation methods to ensure self-report estimates are validated. Verification will be conducted using measures of CO in expired air as recommended by the SRNT Biochemical Verification workgroup [44]. Although cotinine measures provide the gold standard tool for assessing smoking status self-report, the collection of blood, urine or saliva samples with clients in a non-health setting is invasive and impractical. To assess 24-hour smoking cessation, clients will be asked how long ago they last smoked a cigarette, cigar or pipe? (and respond by indicating, last four hours, between 4-8 hours ago, between 8-24 hours ago, more than 24 hours ago). Twenty four-hours is the recommended biochemically verifiable window for CO in expired air [44]. The Jarvis protocol will be used to record expired air CO. A cut-off point of 8 ppm will be used to define a smoker [44]. Measuring CO in expired air has demonstrated high sensitivity and specificity of around 90% for both [44].

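### The primary comparison is a crude chi-square that ignores the blocks of four used to allocate weeks and leaves baseline nicotine dependence to a later, non-primary regression

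*Protocol article*

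**What the plan says.** Under Efficacy of intervention, the article states that "the intervention and control groups will be compared on each of the primary outcomes using chi-square analysis". Abstinence over 24 hours (validated) and over seven days are each tested at one, six and 12 months. The intention-to-treat analysis is described as additional to this primary analysis. A regression comes last: "Multiple logistic regression analyses will be used to compare outcomes between the two intervention groups while adjusting for prognostic variables and potential confounders". Its covariates are listed as "sociodemographic, financial stress, depression, and other variables collected".

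Study Design allocates clients by one-week periods. Recruitment and randomisation adds that "Intervention or control times will be randomly allocated in blocks of four by a computer generated randomisation procedure". Four one-week periods per block is the natural reading, although the article does not say so in those words. No analysis names week, block or calendar time.

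The Background section on the context of smoking and quitting says that "past research has found nicotine dependence is a predictor of failure of attempts to stop smoking". The section Moderating factors measures dependence with the HSI, scored 0 to 6, and says of the whole baseline set: "These items will be collected at baseline, used as part of the intervention print-out, and included in multivariate analysis". So the HSI is used in the analysis, but not in the comparison the plan calls primary.

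**The concern.** Two features of the design are missing from the headline analysis.

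- **Blocking.** It balances the arms over calendar time. An analysis that ignores it leaves differences between periods of the year in the error term.
- **Dependence.** The protocol itself regards it as prognostic and records it before treatment. A crude comparison leaves any difference in dependence between the arms inside the main result.

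The planned regression is a weak substitute. It is not the primary analysis, and its covariate list is open-ended. What is at stake is some precision, and how far the headline estimate is protected against baseline imbalance.

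**Working it through.** **1. The plan's own figure.** The section Sample size gives 5% against 13%, 5% significance, 80% power and 200 per group at 12 months. With a pooled-variance, two-sided test and no continuity correction:

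n = [1.96 × √(2 × 0.09 × 0.91) + 0.842 × √(0.05 × 0.95 + 0.13 × 0.87)]² / 0.08² ≈ 200 per group, with power 0.801.

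The figure reproduces as an unadjusted comparison of independent individuals.

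**2. Events against covariates.** Expected quitters at 12 months are 200 × 0.05 + 200 × 0.13 = 10 + 26 = 36. Moderating factors lists seven sociodemographic items plus dependence, quit attempts, cessation aids, partner smoking, depression and financial stress. That is 13 items, several with more than two categories, so 36 / 13 = 2.8 quitters per item at best.

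**3. Power from adjusting for HSI.** The article gives no prognostic strength, so it is assumed over a range. If the score explains a share R² of outcome variance, n scales by (1 − R²):

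| R² (assumed) | n needed per group | Power at 200 per group |
|---|---|---|
| 0 | 200 | 0.801 |
| 0.02 | 196 | 0.809 |
| 0.05 | 190 | 0.820 |
| 0.10 | 180 | 0.840 |

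Simulated power, crude against HSI-adjusted:

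| Assumed effect of the score | Crude | Adjusted |
|---|---|---|
| Odds ratio per point 0.9 (SD 1.7; 3,000 trials) | 81.0% | 81.7% |
| Odds ratio per point 0.8 | 82.1% | 83.5% |
| Odds ratio per point 0.7 | 81.6% | 83.3% |
| Log-odds per SD −0.3 (2,000 trials) | 80.6% | 80.9% |
| Log-odds per SD −0.5 | 81.9% | 81.9% |
| Log-odds per SD −0.8 | 80.3% | 83.4% |

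Taken together, the gain is about 0 to 4 points.

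**4. Imbalance in HSI.** At 200 per arm, one standard error of the difference in means is √(2/200) = 0.1 SD. With log-odds −0.5 per SD and a mean rate of 9%, the shift is 0.09 × 0.91 × 0.5 × 0.1 = 0.0041, or about 0.4 percentage points against a planned 8.

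For a half-point imbalance on the 0–6 scale, take a true 5% in both arms. The odds are 0.0526. If the intervention arm is 0.5 point less dependent:
- odds ratio 0.8 per point: 0.0526 × 0.8^(−0.5) = 0.0588, which appears as 5.6%
- odds ratio 0.7 per point: 0.0526 × 0.7^(−0.5) = 0.0629, which appears as 5.9%

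With SD 1.7 (assumed), one standard error is 0.17 point, so half a point is 0.5 / 0.17 = 2.9 standard errors under individual-level chance.

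**5. Block.** Assume quit rates vary between four-week periods with SD 0.3 to 0.5 on the logit scale. The block share of outcome variance is roughly 0.09 × 0.91 × 0.3² = 0.007 to 0.09 × 0.91 × 0.5² = 0.020. For the individual-level test this is 0.7% to 2% of variance. Simulated power (2,000 trials, 13 blocks of four weeks, 400 completers), chi-square against a block-stratified test:
- no block effect: 80.3–81.9% against 79.3–80.3%
- block SD 0.3: 81.7% against 80.5%
- block SD 0.5: 80.5% against 80.7%

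So block stratification adds nothing there and can cost 1 to 2 points.

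In a week-level analysis with 400 / 52 = 7.7 completers per week, the same block variance counts for more. Simulated power (3,000 trials) without and with a block term:

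| Setting | Without block | With block |
|---|---|---|
| No block effect | 74.2% | 74.0% |
| Block SD 0.3 | 70.7% | 71.9% |
| Block SD 0.5 | 68.8% | 72.0% |
| Block SD 0.5 and week SD 0.3 | 66.4% | 70.4% |

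A separate week-level simulation ranged from a loss of about 2 points to a gain of about 2. Together the range is −2 to +4.

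**6. Clustering.** Under no effect, with week SD 0.5 on the logit, type I error was about 0.07 for the crude, HSI-adjusted and block-stratified tests alike. None of these three has a week term.

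**The case against.** The best case for the plan is that adjustment is already there. The regression compares the arms, and the HSI belongs to it, so the dispute is only over which of two planned analyses leads. A crude primary test with an adjusted supporting model is a legitimate choice, and the gain from reversing the order is small. That stands as to size. It does not remove the point, because the article fixes the primary test itself, and the existing regression is too large for about 36 quitters to serve as the alternative.

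A second objection also has force. With 36 quitters over about 52 weeks, or 0.7 per week, variance components for week and block will be poorly estimated. The model therefore needs a fallback stated in advance.

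A reader might infer more than the document supports:
- *That dependence is ignored.* It is not; Moderating factors sends it to multivariate analysis.
- *That the crude test loses material power by omitting block.* For the planned individual-level test it does not. The larger figures belong to a week-level analysis, which the plan does not contain, and rest on assumed block variances.
- *That a half-point imbalance in HSI is to be expected.* By individual-level chance it is rare. It becomes plausible mainly if recruitment differs by week type, since the assistant who recruits also knows the week's allocation, or if the expected 30% loss differs by arm. HSI adjustment would remove only the part that the score captures.
- *That efficacy will be reported without an interval.* The section Acceptability says its proportions "will be determined with 95% confidence intervals" and the efficacy section has no such phrase, but a condensed article commonly leaves this detail to the full plan.

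**Conclusion.** The point holds in a limited form. The primary test uses neither the restricted randomisation nor a baseline predictor that the protocol itself endorses, and the adjusted analysis that could use them is neither primary nor well sized. The reason to change is mainly a headline estimate protected against measured imbalance in dependence; any gain in power is modest. All effect sizes rest on assumed prognostic strength and assumed variation between periods, because the article gives neither. The block simulations used a block-stratified test or a block term in a week-level analysis, so they are only a guide to the random-effect model proposed here. The week as unit of randomisation is the more serious matter, and adjusting for HSI and block would not settle it.

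**What to change.** For the 12-month comparison, on which the sample size is based, name one primary model for each primary outcome:
- logistic regression with arm and HSI as a single linear term
- the randomisation block as a random effect, so that 12 block parameters are not spent on about 36 quitters
- the allocated week accounted for as the randomised unit, as a random effect nested in block
- the result averaged over the random effects and the HSI distribution, and given as a standardised risk difference that can be set against the planned 8 points
- a rule, fixed in advance, for non-convergence or a variance estimated at zero

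Keep the crude chi-square as a supporting result and the larger regression as exploratory. State that the blocks consist of four one-week periods, if that is what is meant.

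The cost is a change of wording and somewhat more analysis work. The HSI is already collected, and week and block follow from the recruitment date and the allocation list, so no further data or participants are needed. If quit rates do not differ between periods, the block term may cost 1 to 2 points of power.

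### The analysis of all randomised clients ranks below a primary chi-square that, by implication, covers only clients who return for follow-up; the ranking should be reversed and the missing-as-smoking assumption tested by arm.

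*Protocol article*

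**What the plan says.** In the protocol article, under Efficacy of intervention, "the intervention and control groups will be compared on each of the primary outcomes using chi-square analysis", at one, six and 12 months. The denominator of that test is not named. The same paragraph continues: "In addition to the primary analysis, intention-to-treat analysis will also be undertaken whereby clients who fail to complete follow-up", and completes the rule by saying that "clients who fail to complete follow-up in the study will be considered to be continuing smokers". A covariate-adjusted logistic regression is also planned.

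The Sample size section sets the target as follows: "A sample of 200 participants per group at 12 months will allow detection of a difference in smoking cessation rates of 8% between groups". The calculation is "based on 5% smoking cessation in the usual care group and 13% in the intervention group", and the error rates are given as "at 5% significance level and 80% power". Loss is then allowed for: "Estimating that 30% of the sample are lost to follow-up (10% at each of one, six and 12 months"), so that "290 patients per group will be recruited at baseline".

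Under Recruitment and randomisation, follow-up means going back to the Centre for the survey and a carbon monoxide breath test.

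**The concern.** The analysis that retains lost clients is described as additional to the primary one, so the primary one is presumably restricted to clients with follow-up data. If so, the headline result rests on clients who chose to come back, and that choice is made after randomisation.

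Two features make this more than a formality here. A client who has relapsed may be less willing to return for a breath test than one who has quit. Smoking-related contact also differs by arm. Intervention clients sign a behavioural contract, see a caseworker about smoking and receive phone calls, while control clients receive on-screen advice and a Quitline number. If attendance depends on arm and smoking status together, the completer comparison can show a difference where none exists, or hide one that does. Where the two planned analyses disagree, the plan as written gives precedence to the one that does not preserve randomisation.

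**Working it through.** **1. The plan's own figure.** Inputs from Sample size: p1 = 0.05, p2 = 0.13, 5% significance (taken as two-sided), 80% power. The pooled formula without continuity correction, with mean rate 0.09, is:

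n = [1.96 × √(2 × 0.09 × 0.91) + 0.842 × √(0.05 × 0.95 + 0.13 × 0.87)]² / 0.08² ≈ 200 per group.

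The stated 200 is reproduced (power 80.1%). Inflating for loss gives 200 / 0.70 = 286, against 290 stated. So 5% v 13% was powered on clients still present at 12 months.

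**2. How many clients are left out.** Reading the loss as 10% of those recruited at each visit, each group keeps 290 × 0.90 = 261 at one month, 290 × 0.80 = 232 at six months and 290 × 0.70 = 203 at 12 months. At 12 months 87 per group, 174 of 580 in all, would be outside the primary test. The expected quitters among completers are 203 × 0.05 ≈ 10 and 203 × 0.13 ≈ 26.

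**3. Effect of selective attendance when there is no true effect.** The documents give no attendance by arm or smoking status, so every attendance rate below is an assumption. With true quit rate q = 5% in both arms, quitters attending at rate a and continuing smokers at rate s:

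- completer rate = q·a / [q·a + (1 − q)·s]
- missing-as-smoking rate = q·a

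| Assumed attendance (quitters / smokers) | Completers, control v intervention | Missing as smoking, control v intervention |
|---|---|---|
| Control 90/75, intervention 90/60 | 5.9% v 7.3% (+1.4 points) | 4.5% v 4.5% |
| Control 90/60, intervention 90/75 | 7.3% v 5.9% (−1.4) | 4.5% v 4.5% |
| Control 90/70, intervention 90/50 | 6.3% v 8.7% (+2.3) | 4.5% v 4.5% |
| Control 60/60, intervention 80/80 | 5.0% v 5.0% | 3.0% v 4.0% (+1.0) |
| Control 75/60, intervention 90/75 | 6.2% v 5.9% (−0.2) | 3.75% v 4.5% (+0.75) |

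First row, control: 0.05 × 0.90 = 0.045; 0.95 × 0.75 = 0.7125; 0.045 / 0.7575 = 5.9%. Intervention: 0.045 / (0.045 + 0.95 × 0.60) = 0.045 / 0.615 = 7.3%.

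With 290 randomised per group, the chance that the completer test falsely favours the intervention is about 8% in the first row and about 13% in the third, against a nominal 2.5%.

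**4. Power if the ranking is reversed.** This uses the same pooled formula with 290 per group.

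- If 5% and 13% are rates among completers and loss is 30% in each arm: 0.70 × 5% = 3.5% and 0.70 × 13% = 9.1%, a difference of 5.6 points. Power is 79.4%, against 80.1% on 200 completers (80.6% on 203).
- If 5% and 13% already count missing clients as smokers: power is 92.2%.

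Both figures ignore any clustering from allocation by week.

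**The case against.** The strongest reply is that the safeguard is already planned. The all-randomised analysis stands in the same paragraph, so a reader of the results could compare the two. This is right. A reader might infer that the randomised comparison is lost for the main conclusion, but the documents do not support that: it is specified in advance and only ranked second.

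The restriction to completers is also inferred. No sentence states it, and inflating a sample size for loss is routine whichever analysis is primary, so the sizing is only supporting evidence. The inference still stands, because the analysis that keeps lost clients is the one described as additional.

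The 30% loss applies at 12 months only; about 10% and 20% are implied at the two earlier time points, which are also tested.

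The most substantive objection is that missing-as-smoking is not a neutral replacement. The first three rows of the table hold quitter attendance equal across arms, which is the condition under which that rule shows no bias when there is no true effect. In the last two rows quitters are retained differently, and missing-as-smoking is the more biased analysis, in favour of the intervention. This stands, and it shapes the fix.

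Finally, the contrast in contact concerns smoking care. The intervention is added to usual counselling visits, so control clients may also stay in touch with the Centre.

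**Conclusion.** The concern holds as a matter of rank. The protocol itself fixes the order of the analyses, so this is not a detail left to a statistical analysis plan. The primary test is, by clear implication, a comparison of clients who return, and its result can be biased in either direction if attendance depends jointly on arm and smoking status. Under the assumed attendance rates the spurious difference is about 1.4 to 2.3 points in size, against a design difference of 8 points. If attendance does not depend on arm and smoking status together, this bias does not arise.

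Two stronger readings are not supported. One is that the completer analysis must favour the intervention: swapping the arms reverses the sign. The other is that counting missing clients as smokers removes the problem: it does so only if quitters are retained equally in both arms. The point should be fixed, but it is not a fatal flaw, because the analysis that should lead is already in the plan.

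**What to change.** 1. In the efficacy analysis section, make the comparison of all randomised clients (290 per group, missing counted as smoking) primary, and name that denominator. Move the completer analysis to sensitivity.
2. State that missing-as-smoking is an assumption that can itself be biased when quitters are retained differently by arm. Add one sensitivity analysis, such as multiple imputation, that lets missingness differ by arm and smoking status.
3. In the sample size section, say whether 5% v 13% are completer or all-randomised rates. If completer rates, restate them as about 3.5% v 9.1% under equal 30% loss (power about 79%); if all-randomised rates, power is about 92%.

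The cost is small: re-ordered labels, one clarified pair of rates and a little more analysis, with no extra visits or data collection. Reported quit rates will be lower than completer rates. Any allowance for clustering by week is a separate matter.
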